### Participant recruitment

Participants will be recruited from the stroke services of three National Health Service (NHS) Hospital Trusts and community therapy services, covering an area with a population of 918,300 [30]. This trial intends to recruit 50 participants over a period of 15 months. Eligibility criteria are designed to be as inclusive as possible to promote the applicability of the evidence to service delivery.

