### Outcome measurement

Baseline assessments will be conducted within 1 week of recruitment and before randomization. Outcome assessment will be performed at 7 weeks post-randomization, and follow-up assessments at 3 and 6 months after randomization. The assessments will be carried out in the participant’s home by an assessor who is blinded to group allocation and who is trained in the assessment procedures. All of the following assessments will be undertaken at all four time points: ARAT, WMFT, Motor Activity Log (MAL), and Stroke Impact Scale (SIS). The health and social care questionnaire and the CSI will be undertaken only at the follow-up assessments.

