### Randomization

Participants will be randomly allocated to the intervention or to the usual care groups in a 1:1 ratio after baseline assessment. Randomization will occur via an independent internet-based service, and the procedure will use minimization to balance time since stroke, severity of upper-limb impairment, and group numbers between the two arms. Time since stroke will be categorized as less than or equal to 3 calendar months post-stroke, or more than 3 calendar months post-stroke. This 3-month cut off was chosen to balance between groups the number of participants within 3 months of stroke, who might be recovering at a faster rate [46]. Baseline severity will be categorized using scores on the ARAT in three subgroups defined by Morris *et al*. [47] (group 1: score 0 to 3; group 2 score 4 to 28; group 3 score 29 to 56).

The data for the randomization procedure will be entered by the trial manager. He will have no influence over the allocation to group because the randomization procedure is independent, and he will not be involved in measuring outcome. Post-randomization, the trial manager will contact the patient and any NHS services involved in the patient’s care to inform them of the treatment allocation.

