### Data analysis

As this is a feasibility study to test the levels of recruitment and retention of participants, and completeness of data that can be expected within a definitive multicenter trial, there will be no formal statistical testing, and results will instead be summarized using descriptive statistics.

Analysis of the centrally held screening log data will lead to a description of the characteristics of the recruited sample against the target population, and the percentage of refusals at the recruitment stage. Recruitment rates per month for each site will be determined. The number of withdrawals and reasons for withdrawal from the study will be assessed.

Compliance with the RTG intervention will be assessed by the number and duration of physiotherapy visits and the proportion of participants completing the 6-week intervention. The frequency of use of the exercises, number of repetitions, and duration of practice of each exercise, both within the physiotherapy sessions, and the independent practice will be summarized and compared with the intended exercise frequency and content. The frequency and content of the treatment received by each group will be summarized, as will the incidence of expected AEs and serious AEs. Responses to the participant questionnaire about the RTG training will be synthesized and examined to determine if any changes should be made to the intervention.

Completeness of outcome data will be determined, and data for each of the endpoints will be summarized; the mean differences between the arms, with their confidence intervals, will be presented. Assessment of the sample scores on the outcome measures, combined with a summary of participant preference for ARAT and WMFT, will be carried out to determine which arm function test should be used as the primary outcome measure for a phase III trial. Sample sizes for a subsequent phase III trial will be calculated, based on observed changes from baseline in performance, for both the control and intervention groups.

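### As described, the between-arm intervals and the phase III sizing do not use baseline scores or the minimization factors as covariates, which costs precision by an amount that depends on an unstated correlation

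*Protocol article*

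**What the plan says.** The Data analysis section is deliberately descriptive: "there will be no formal statistical testing, and results will instead be summarized using descriptive statistics". For the endpoints it adds that "the mean differences between the arms, with their confidence intervals, will be presented". It does not say whether the difference is in final score or in change, names no model or covariate, and gives no confidence level. The closing sentence of the same section bases the phase III sample size on changes from baseline observed in each arm. Objective 6 makes that calculation one of the trial's aims.

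The design does use baseline information. The Randomization section says that "the procedure will use minimization to balance time since stroke, severity of upper-limb impairment, and group numbers between the two arms". Severity enters as three ARAT bands ("group 1: score 0 to 3; group 2 score 4 to 28; group 3 score 29 to 56") and time since stroke as up to or over 3 calendar months. The Outcome measurement section has ARAT, WMFT, MAL and SIS recorded at baseline and at all three later assessments. The Caregiver Strain Index and the resource-use questionnaire are recorded at follow-up only.

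**The concern.** Minimization on ARAT band removes much of the chance difference in baseline severity between arms. An unadjusted standard error does not register this: it still counts the variation in severity between patients as noise in the comparison. The interval is then wider than the design warrants and covers more often than its stated level. A change score removes part of the baseline variation, but it fixes the coefficient on baseline at one, where a regression would estimate it.

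What is at stake is precision and planning. With about 25 patients per arm the intervals are wide in any case, and unnecessary width makes the by-arm results less informative. The variance passed to the phase III calculation would also exceed what a baseline-adjusted definitive analysis needs.

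**Working it through.** The plan states no SD, correlation, precision target or power, so there is no figure of its own to reproduce. The check compares three ways of forming the same interval.

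**Inputs from the article.** "This trial intends to recruit 50 participants over a period of 15 months"; 1:1 allocation, so 25 per arm; minimization on three ARAT bands, two time bands and group numbers.

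**Assumptions.** 95% level, equal SDs in both arms and at both times, and baseline to follow-up correlation r varied because the article gives none.

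**Half-widths in SD units, 25 per arm**

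- Final score: t(48) × √(2/25) = 2.011 × 0.2828 = 0.569.
- Change score: 0.569 × √(2(1 − r)).
- Adjusted for baseline: t(47) × √(2/25) × √(1 − r²) × √(1 + 1/46), the last term being a small-sample factor. At r = 0.7 this is 2.012 × 0.2828 × 0.714 × 1.011 = 0.411.

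**Sample size inflation.** Required n is proportional to variance. Change-score variance over adjusted variance is 2(1 − r)/(1 − r²) = 2/(1 + r).

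| r | Final score | Change score | Adjusted | Final / adjusted | Change / adjusted | Phase III n, change / adjusted |
|---|---|---|---|---|---|---|
| 0.5 | 0.569 | 0.569 | 0.498 | 1.14 | 1.14 | 1.33 |
| 0.7 | 0.569 | 0.441 | 0.411 | 1.38 | 1.07 | 1.18 |
| 0.8 | 0.569 | 0.360 | 0.345 | 1.65 | 1.04 | 1.11 |
| 0.9 | 0.569 | 0.254 | 0.251 | 2.27 | 1.01 | 1.05 |

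With 20 per arm, to allow for loss, the final/adjusted ratios are almost the same: 1.14, 1.38, 1.64 and 2.26.

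**Coverage under minimization.** 4,000 trials of 50 patients were simulated at each r. Baseline was normal and cut into three bands, time since stroke had two equal bands, and the favoured arm was chosen with probability 0.8. There was no treatment effect and no loss. The adjusted model used baseline and time band.

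| r | Final score | Change score | Adjusted |
|---|---|---|---|
| 0.5 | 96.5% | 96.3% | 94.7% |
| 0.7 | 98.0% | 95.9% | 94.8% |
| 0.8 | 98.9% | 94.9% | 94.1% |
| 0.9 | 99.5% | 96.0% | 95.5% |

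Monte Carlo error is about √(0.95 × 0.05/4000) = 0.3 percentage points. The simulated width ratios of final to adjusted agree with the formulas. At r = 0.5 the ratio is 1.132/0.984 = 1.15, and at r = 0.9 it is 1.138/0.497 = 2.29.

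**Reading the two tables together.** The two losses move in opposite directions. A high r makes final scores inefficient and change scores nearly efficient; a low r does the reverse. The 127% excess width and the 33% inflation therefore cannot occur in the same trial on the same outcome.

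**The case against.** The strongest reply is that the text never says unadjusted. A covariate-adjusted mean difference also fits the words, the analyses are assigned to a registered clinical trials unit, and a full protocol or SAP that is not shown may name the covariates. A reader might infer that the authors decided to ignore baseline; the article does not support that. What stands against the reply is narrower. The comparison is placed within a descriptive analysis with no model mentioned, and its plain reading is an unadjusted one. The use of change from baseline for the phase III size is explicit, whatever the SAP adds about intervals.

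A reader might also infer that the intervals are far too wide. That needs both a final-score comparison and a correlation of roughly 0.8 or more, and the article gives neither. Some features point to a high correlation: eligibility spans a wide range of impairment, and the article cites ARAT test–retest reliability of 0.99. Others point the other way: the Randomization section expects patients within 3 months of stroke to recover possibly faster, which would weaken it. The only outcome scale named in that section is change from baseline, and on that scale the loss is small at high correlations.

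Finally, the error is conservative, no test or progression rule rests on the interval, and no precision target is set for it to miss. All of this stands, and it limits the point to a loss of efficiency.

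**Conclusion.** The point holds as a conditional one about efficiency. As described, neither the between-arm differences nor the phase III sizing uses baseline as a covariate or the factors on which the trial minimizes.

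- On final scores, intervals are about 14% (r = 0.5), 38% (0.7) or 127% (0.9) wider than adjusted ones, with coverage of about 96% to 99% for a nominal 95%.
- On change scores, the excess is about 14% at r = 0.5 and 1% at r = 0.9, with coverage close to nominal.
- Change-based sizing inflates phase III n by 33% at r = 0.5, falling to 5% at r = 0.9, if the definitive trial is analysed with baseline adjustment.

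These figures rest on an assumed correlation, equal SDs, normal scores and an assumed minimization probability. The ARAT is a bounded ordinal total, so the real figures will differ. No bias arises and no stated target is missed. If an unseen SAP already adjusts, the interval part falls away and the sizing part remains.

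**What to change.** For ARAT, WMFT, MAL and SIS, present the between-arm difference and its confidence interval at each time point from a linear model. Adjust it for that outcome's baseline value, baseline ARAT and time since stroke (up to or over 3 months). For ARAT the first two are a single term. Keep raw means and SDs by arm as description. Report the residual SD and the baseline to follow-up correlation for each outcome, and use these as the variance inputs to the phase III sample size. The phase III team can then size for whichever analysis it adopts.

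The cost is a few words of analysis text. Every covariate is already collected before randomization, no visit or measurement is added, and the analysis remains free of formal testing.

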### Study objectives

The aims of this feasibility trial are as follows.

1. To determine the characteristics of the sample entering the feasibility trial for its representation of the target population and to determine the most appropriate primary outcome measure for the sample, that is, the Action Research Arm Test (ARAT) or the Wolf Motor Function Test (WMFT).

2. To estimate identification and recruitment rates for the trial across multiple sites.

3. To determine the frequency and content of upper-limb treatment delivered to both the intervention and control groups.

4. To estimate the adherence of RTG group participants to the prescribed schedule.

5. To estimate the completeness of outcome data.

6. To calculate sample sizes for a subsequent definitive trial, based on measured changes in performance for both the control and intervention groups.

7. To collect and synthesize the views from participants in the intervention group to determine acceptability of the RTG therapy.

8. To determine the frequency of AEs in both groups.

9. To collect data on health and social care resource use to inform data-collection methods for an economic evaluation in the subsequent definitive trial.

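### The definitive trial's sample size is to be based on the changes observed in each arm, with no other source for the target difference, although about 25 per arm estimates that difference only to within about 0.57 SD.

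*Protocol article*

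**What the plan says.** The protocol article states the basis of the definitive trial's size twice. Aim 6 under Study objectives reads: "To calculate sample sizes for a subsequent definitive trial, based on measured changes in performance for both the control and intervention groups". The Data analysis section repeats it: "Sample sizes for a subsequent phase III trial will be calculated, based on observed changes from baseline in performance", again for both groups.

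The same section limits the analysis to description: "there will be no formal statistical testing, and results will instead be summarized using descriptive statistics". It adds that "the mean differences between the arms, with their confidence intervals, will be presented", but does not connect those intervals to the sample-size calculation.

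On the size of this trial, Participant recruitment says "This trial intends to recruit 50 participants over a period of 15 months", and Randomization says "Participants will be randomly allocated to the intervention or to the usual care groups in a 1:1 ratio after baseline assessment". That gives 25 per arm before any loss.

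The article names no minimum important difference or other target, on either the Action Research Arm Test (ARAT) or the Wolf Motor Function Test (WMFT). Under Outcome measurement, participants are asked which measure better reflects meaningful change, but that informs the choice between the two tests and does not set a target.

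**The concern.** A sample size for comparing two means needs a target difference and an SD. A trial of this size estimates the SD usefully but the treatment difference poorly. If the changes in the two arms are the basis and nothing else supplies the target, the difference between those changes becomes the target. The required size varies with the inverse square of that difference, so error in the estimate is strongly magnified.

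An estimate that is high by chance gives a definitive trial with little power. One that is low by chance gives a trial too large to run, and one in the wrong direction gives no size at all. Informing the sample size is a purpose named in the Abstract and a numbered aim, so the fault affects a main product of the study.

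**Working it through.** **Nothing to reproduce.** The article gives no size, alpha, power, SD or target difference for the definitive trial.

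**Inputs from the article.** 50 participants, allocated 1:1, so n = 25 per arm.

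**Assumptions.** Two-sided 5% and 80% power; true standardised difference d = 0.4, with 0.3 and 0.5 as the range; normally distributed outcomes; no loss to follow-up.

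**1. Precision of the observed difference.** This depends only on n.
- SE = sqrt(2/25) = 0.283 SD.
- 95% half-width = t(0.975; 48 df) × SE = 2.011 × 0.283 = 0.57 SD. With 20 per arm it is 0.64 SD.
- The unit is the SD of whatever is analysed, so the result applies equally to change scores.

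**2. What one such interval implies for planning.** Suppose the observed difference is 0.4 SD. Its interval is 0.4 ± 0.57, or -0.17 to 0.97. The upper limit leads to 17 per arm; the lower limit gives no finite size.

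**3. Size needed.** n per arm = 2 × ((1.960 + 0.842)/d)². At d = 0.4 this is 2 × 7.849/0.16 = 98.1, or about 98 per arm.

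**4. Chance of no usable estimate.** P(observed difference ≤ 0) = Φ(-0.4/0.283) = Φ(-1.414) = 7.9%.

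**5. Sizing from the observed difference.** This was simulated by drawing the difference and the SD, computing n per arm from their ratio, and then computing true power at d = 0.4. Among positive estimates:
- the planned size has a 10th to 90th percentile range of about 25 to 895 per arm (the upper figure moves by a percent or two between runs);
- about 30% of plans have true power below 50%.

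A hand check agrees. Power falls below 50% when the observed d exceeds the true d by a factor of 2.802/1.960 = 1.429, so above 0.572. Ignoring error in the SD, P = 1 - Φ((0.572 - 0.4)/0.283) = 1 - Φ(0.61) = 27%. Dividing by the 92.1% of positive estimates gives 29 to 30%.

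**6. Sizing from a fixed target of 0.4 with only the SD taken from this trial.** The planned size is 98.1 × chi-square(48)/48.
- The 10th to 90th percentile range is about 74 to 125 per arm.
- Power falls below 50% only if the variance estimate is under (1.960/2.802)² = 0.489 of the truth. P(chi-square(48) < 23.5) = 0.1%.

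**7. Range over the assumed effect.**

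| True d | Needed per arm | Observed ≤ 0 | Power < 50%, observed difference as target | Power < 50%, fixed target |
|---|---|---|---|---|
| 0.3 | 174 | 14% | 38% | 0.1% |
| 0.4 | 98 | 8% | 30% | 0.1% |
| 0.5 | 63 | 4% | 25% | 0.1% |

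The two power columns are shares of plans; the first is conditional on a positive estimate.

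**The case against.** The best defence is that neither sentence says outright that the observed difference will be the target. A calculation on change scores also needs the SD of change in each arm, and "based on observed changes from baseline in performance, for both the control and intervention groups" could cover that use. Both passages speak of sizes in the plural, which fits several scenarios or one calculation per candidate measure. This stands in part: the use of the observed difference is an inference. It is still the more natural reading, because the text names the changes themselves, in both arms, and supplies no other target. If only the SD was meant, the same rewording is needed to say so.

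It can also be said that confidence intervals will be reported, so the imprecision will be visible, and that the later trial must justify its own size. Both are true. They limit the harm, but they do not change what aim 6 commits to.

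Three stronger readings are tempting, and the article does not support them.
- A reader might infer that the measure with the luckier between-arm difference could be chosen and then used for sizing. The Data analysis section says "Assessment of the sample scores on the outcome measures, combined with a summary of participant preference for ARAT and WMFT, will be carried out", and Outcome measurement bases the choice on the sample's level of functioning and on participants' preferences. Neither refers to a difference between arms.
- A reader might infer further bias from going ahead only when the estimate looks good. The article contains no such rule.
- A reader might point out that about 55% of plans at d = 0.4 have true power below 80%. That figure does not separate the two approaches: a fixed target with an uninflated SD gives 53%, since P(chi-square(48) < 48) = 0.527. The share below 50% does separate them.

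There is also no contradiction between doing no formal testing and using the data to inform a sample size.

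**Conclusion.** The point holds. As worded, aim 6 and the Data analysis section make the observed arm changes the basis of the definitive trial's size and leave the target difference without any other source. The half-width of 0.57 SD follows from the planned 25 per arm alone. The consequences for planned size and power rest on the assumed effect, alpha and power, and on reading the observed difference as the target. Over true differences of 0.3 to 0.5, between 38% and 25% of plans with a positive estimate would have true power below 50%, against about 0.1% with a fixed target. No participant, estimate or conclusion of this feasibility trial is affected; the cost falls on the definitive trial.

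**What to change.** Reword aim 6 and the matching Data analysis sentence to say:

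1. The target difference will be a justified minimum important difference on the chosen measure, fixed before any by-arm results are seen.
2. This trial will supply the SD (of change, or residual given baseline, pooled within arms), the baseline to follow-up correlation and attrition.
3. The uncertainty of the SD will be allowed for, for example by an upper confidence limit. As one option, a one-sided 80% limit multiplies the variance by 48/chi-square(0.20; 48 df) = 1.21 with 50 participants, or 1.24 with 40. Other allowances would also serve.
4. The observed difference and its confidence interval will be reported only as a check that the target is not excluded.

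The change is to analysis wording alone; it alters no visit, assessment or dataset. The article reports recruitment as still under way, so the target could be fixed before by-arm results exist. The downside is that the stated size of the definitive trial may come out larger.

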### Trial monitoring and management

The trial manager will manage the day-to-day running of the study. Before the study commences, training sessions for clinical staff involved at each site will be organized by the UWE research team. These sessions will ensure that personnel involved fully understand the research protocol, delegation log, and standard operating procedures for the study.

The UWE research team will meet regularly (ideally fortnightly) throughout the trial. The trial steering group, CI and trial manager will have a teleconference every 4 months to discuss progress, including recruitment, withdrawals, treatment compliance, and AEs. The steering group will provide advice on amendments to protocol if necessary.

The Bristol CTEU, a clinical trials unit registered with the UK Clinical Research Collaboration, will specify the randomization scheme, develop and maintain the study database, and carry out trial analyses in collaboration with the investigators. An independent data monitoring and safety committee will not be convened for this pilot study, as there is very low risk of intervention-related AEs and a short recruitment, intervention, and follow-up period.

### Ethical considerations

The study has been approved by the National Research Ethics Service, South West Southmead Research Ethics Committee (REC) (ref number: 10/H0102/83) and the sponsor’s REC at the Faculty of Health and Life Sciences, UWE, Bristol. The study has been approved by the Research and Development (R&D) departments responsible for each site. This study will be conducted in accordance with the principles of the International Conference for Harmonisation of Good Clinical Practice (ICH GCP) guidelines [55] and the Research Governance Framework for Health and Social Care [56]. Information about possible benefits and risks of participation will be described in the patient information sheets. Any amendments to the trial documents must be approved by the sponsor before submission to the REC and R&D departments.

The study will be monitored and audited in accordance with the sponsor’s policy, which is consistent with the Research Governance Framework [56]. All study-related documents will be made available on request for monitoring and audit by the sponsor or funder and the relevant REC. This is a UWE-sponsored research study, working in collaboration with NHS trusts. The University's Clinical Trials insurance cover provides either legal liability cover or non-negligent/no-fault compensation cover.

